## Abstract

**Background:**

Given the risk of progression to dementia ranging from 6 to 44.8% over approximately 4 years of follow-up, nonpharmacological multicomponent interventions are emerging as promising strategies to improve or maintain cognitive function and quality of life in individuals with mild cognitive impairment (MCI). This pilot study aims to evaluate the feasibility and potential efficacy of a multicomponent and transdisciplinary intervention focused on the dyad of older adults with MCI–family study partner to promote cognitive function in older adults.

**Methods:**

A pilot, randomized, controlled, and double-blind clinical trial will be conducted with 102 dyads consisting of an older adult with MCI and their family study partner. The participants will be randomly assigned to two groups: the intervention group (INTERCOG) and the control group. The INTERCOG group will receive a 12-week home-based intervention (twice weekly) with the support of a healthcare professional. The intervention components consist of cognitive training and stimulation, nutritional counseling, and physical exercises. Simultaneously, family members will participate in a training program on care and self-care. The control group will receive an Enhanced Standard of Care with educational messages on infection prevention. The feasibility of the study will be assessed through an analysis of recruitment, data collection, intervention acceptability, and implementation challenges; also, changes in global cognition and changes in specific cognitive domains will be measured as exploratory results. Secondary outcomes will include changes in health-related quality of life, caregiver burden, social support for family members, as well as changes in functional independence, frailty, physical capacity, family functioning, and nutritional status in patients, with follow-up at 3, 6, and 9 months. In a subsample of 40 participants, the diversity of the gut microbiota will be characterized, and the frequency of the APOE-ε4 allele will be determined.

**Discussion:**

Multicomponent and transdisciplinary interventions focused on the family member–patient dyad have the potential to optimize cognitive outcomes and quality of life. This pilot study will allow us to identify key aspects of the feasibility and potential efficacy of INTERCOG intervention, crucial information for the design of future larger-scale studies.

**Trial registration:**

NCT06408103. December 6, 2024, at clinicaltrials.gov. In recruitment.

**Supplementary Information:**

The online version contains supplementary material available at https://doi.org/10.1186/s40814-026-01871-1.

## Background

Population aging is expected to lead to an increase in chronic noncommunicable diseases, posing a challenge to health systems [1]. In the Americas, the global burden of dementia is projected to rise from 6.86 million cases in 2020 to 19.3 million in 2025, an escalation of more than threefold increase [2]. This projection underscores the need to implement comprehensive interventions that preserve cognitive function, prevent or slow the progression to dementia, and engage families, multiple sectors, and public policy [3].

Interventions focusing on individuals with mild cognitive impairment (MCI) are crucial, given that progression to dementia can occur in 6 to 44.8% of cases, with an average follow-up of 3.7 years in low- and middle-income countries [4]. Preventing this progression is vital in countries such as Colombia, where the prevalence of MCI in the elderly population is 17.93% [5]. This risk of progression is significantly compounded by existing comorbidities, nearly tripling in uncontrolled diabetes (HR = 2.87, 95% CI 1.20–6.85) and doubling with cardiac comorbidities (HR = 2.27, 95% CI 1.21–4.25) [6]. These figures underline the necessity of developing culturally relevant interventions that optimize cognitive function and mitigate progression to dementia by linking the prevention and control of noncommunicable chronic diseases. Furthermore, it is essential to integrate family study partners as active participants in the management process. Recent evidence indicates that caregiver burden is already present in family members of individuals with MCI and is significantly associated with the patient’s neuropsychiatric symptoms and the dyad’s quality of life, rather than being exclusively dependent on functional decline [7]. This integration is decisive because of the high caregiver burden often experienced by those caring for individuals with cognitive disorders, which negatively impacts their quality of life and can exacerbate the patient’s cognitive decline [8]. Multicomponent interventions have demonstrated efficacy in reducing the burden and increasing the social support of caregivers of patients with Alzheimer’s disease (AD) [9, 10].

Nonpharmacological multicomponent interventions (NPMIs) have been shown to be superior to single-domain interventions in improving cognition in patients with MCI. A meta-analysis of 28 studies published between 2011 and 2021 concluded that multidomain interventions had superior effects to single interventions in terms of global cognition (standardized mean difference SMD = 0.41, 95% CI, 0.23–0.59; *p* < 0.001) and other cognitive domains, such as executive functions, verbal fluency, and memory; however, high variability was observed in terms of the combination of interventions, duration, and frequency [11]. Similarly, another meta-analysis of 8 clinical trials indicated a moderate effect of NPMIs on global cognition, with a moderate effect for the Mini-Mental State Examination (MMSE) (SMD = 0.249, 95% CI, 0.067–0.431). Importantly, compared with cognitive-based interventions, studies that combine cognitive and physical interventions have shown superior effects on global cognition [12].

While recent years have seen the emergence of anti-amyloid immunotherapies as a potential pharmacological approach to modify MCI progression, their clinical implementation remains limited by high costs, rigorous eligibility requirements, and safety monitoring needs. Given the limited accessibility of these treatments in many global contexts and the significant risk of progression to dementia, the identification of modifiable risk factors is crucial for intervention.

Nutritional intake and diet are recognized lifestyle elements that are linked to the risk of MCI and AD [13]. Nutritional intervention has become a nonpharmacological approach, either through the intake of specific nutrients or dietary patterns that have protective effects [14, 15]. This protective effect is likely mediated by various biological pathways involved in cognitive impairment, such as amyloid-beta deposition, inflammation, and oxidative stress, which justifies the inclusion of nutritional counseling as a key component in a multicomponent intervention aimed at the management of MCI [15]. Additionally, nutritional interventions could modulate the composition of the gut microbiota, as various studies have shown differences between individuals with MCI/AD and healthy older adults [16, 17].

In line with the above, and despite the scientific support for NPMIs, the need to determine their optimal combination and dosage persists. This underscores the importance of comprehensive and multicomponent interventions that integrate physical activity, rehabilitation or cognitive stimulation, and nutritional counseling, also involving the family member as a future caregiver and a key factor for adherence. Therefore, this study aims to evaluate the potential efficacy and feasibility of a multicomponent and transdisciplinary intervention directed at the family study partner–older adult dyad with MCI to optimize cognitive function. For this purpose, the efficacy of the NPMIs on global and domain-specific cognitive function in patients with MCI will be explored. Additionally, the feasibility, acceptability, and adherence to the intervention will be examined. Additionally, changes in the health-related quality of life of the dyad, social support, independence, frailty, physical capacity, family cohesion and adaptability, nutritional status, and, in a subgroup, potential changes in the composition of the gut microbiota will be evaluated.

## Methods

### Design

We will conduct a randomized controlled pilot trial, parallel group, with an allocation ratio of 1:1, and investigator/evaluators will be blinded, following the SPIRIT guidelines and CONSORT extension for pilots [18, 19].

### Participants and eligibility criteria

Dyads, consisting of a patient diagnosed with MCI and a family study partner, who are both residents of four cities in the metropolitan area of Bucaramanga in Santander, Colombia, will be selected to participate in this study. Patients aged 55 years or older were required to have an MCI diagnosis made by a psychiatrist or neurologist and confirmed by neuropsychological evaluation, defined as a clinical stage that corresponds to the Mild Neurocognitive Disorder (mNCD) category in the DSM-5 [20] and ICD-11 (Code 6D81) [21]. Following the international consensus, the operational diagnosis was based on (1) objective evidence of modest decline in one or more cognitive domains and (2) preserved independence in daily life activities, although these may require greater effort or compensatory strategies [22]. In addition, they needed to have basic reading and writing skills, not present uncorrected sensory impairments (auditory or visual), have no limitations for physical activity or mobility, have a Barthel Index ≥ 80, a body mass index ≥ 18.5, tolerate oral intake, and be vaccinated against COVID-19 to mitigate the risk of potential infections during home-based intervention visits.

The exclusion criteria for patients in the study are as follows: a clinical history of congenital intellectual disability or psychosis; the presence of central nervous system pathologies that affect cognitive function; a diagnosis of untreated psychiatric disorders; clinically significant systemic diseases, including chronic kidney disease, hepatopathies, and lung diseases requiring oxygen therapy; active cancer treatment with chemotherapy; problematic use of alcohol, tobacco, or psychoactive substances; the need for nutritional support via oral, enteral, or parenteral routes; and the identification of low exercise tolerance, vertigo, or medical restriction for performing moderate to vigorous intensity physical activity. The study elimination criteria include institutionalization of the participant for a period longer than 1 week during the intervention phase, death of the participant during the intervention phase, and nonattendance at 34% or more of the scheduled sessions with professional accompaniment. The inclusion criteria for family study partner are as follows: (1) aged >18 years; (2) literate (basic reading/writing proficiency); and (3) a consanguineous or non-consanguineous kinship with the participant.

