### Intervention

INTERCOG is a nonpharmacological, multicomponent, and transdisciplinary intervention with a focus on the patient-family dyad. Its components include cognitive training and stimulation, physical training, nutritional counseling, and support for the family study partner. Patients assigned to the intervention group will receive the NPMI INTERCOG for 12 weeks, twice weekly home-based sessions and once weekly independent work session consisting of 10–30 min of daily walking and complete homework.

The home-based sessions will include cognitive training/stimulation, physical training, and nutritional counseling. For their part, family study partners will receive weekly training at a university institution for 12 weeks. The intervention structure for the dyad is described in Table 1. To facilitate the intervention process, two workbooks were developed (one for patient and another for family member) [23, 24], as were video recordings to guide physical activity and nutritional recommendations [25]; detailed 12-week schedule of the intervention is provided in Supplementary Table S1. A distinctive feature of the INTERCOG program is its home-based delivery model. By conducting the intervention within the participants’ domestic environment, we aim to reduce geographical and economic barriers to care—such as travel time and transportation costs—which are often deterrents for older adults and their family study partners in regions like Santander.

**Table 1 Tab1:** The nonpharmacological, multicomponent intervention INTERCOG for MCI focuses on the patient–family dyad, Bucaramanga, and the metropolitan area, Santander, Colombia, 2025

Component	Target domains/clinical goals	Enhanced specific activity examples	Tailoring and progression
Cognitive	Executive function, memory (episodic/working/sensory), attention, calculation, and orientation	Ecological task planning: organizing medication schedules and grocery lists. Neurocognitive training: life-history reconstruction (autopsychic orientation), trail making (visual attention), and arithmetic logic puzzles for mental calculation	3 levels of difficulty per activity (scaffolded progression). Tasks advance from simple stimulus identification to complex multi-step problem solving

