Physical	Aerobic capacity, muscular strength, static/dynamic balance, and joint mobility and simultaneous dual task	Dual-task integration: performing verbal fluency tasks while walking. Proprioceptive challenge: lower-limb strength exercises (e.g., squats) performed with eyes open/closed to increase neuro-vestibular demand. Standardized 21-video series for strength, gait, and balance	Progression by intensity: workload is monitored via the Modified Borg Scale, increasing from a baseline of intensity 4 (month 1) up to intensity 8 (month 3)
Nutritional	Glycemic control, brain-health nutrients (omega-3/antioxidants), and dietary habit modification	Interactive nutritional workshops: “cooking laboratories” for preparing functional foods (e.g., quinoa, flaxseed). Behavioral coaching: strategies for sugar reduction and identifying ultra-processed vs. whole-grain carbohydrates	Shift from theory to practice: transitions from basic macronutrient education to the implementation of Mediterranean-style neuroprotective diets in daily life
Familiar	Psychoeducation, communication skills, and prevention of caregiver burden	Empowerment sessions: family reorganization workshops, conflict resolution training, and relaxation therapies. Technological literacy: training on the use of health-monitoring apps and virtual support networks	Focus on resilience: moves from initial program induction and emotional support to the establishment of long-term sustainable caregiving routines

The control group, in addition to usual care, will receive weekly information on the prevention of infectious diseases on their mobile devices. This material, similar to that available online, will be provided as an Enhanced Standard of Care (ESOC) (Supplementary Table S2). Once the study is completed, participants in the control group will receive an intensive 1-week version of the NPMI INTERCOG, as well as the workbooks for the patient and the family member.

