### Intervention fidelity and standardization

The INTERCOG intervention will be delivered by a trained multidisciplinary team (nurses, psychologists, physiotherapists, and speech-language pathologists). To minimize inter-interventionist variability, the program utilizes two registered workbooks [23, 24], which contain all standardized cognitive, nutritional counseling, physical, and familiar activities. Prior to the trial, all interventionists will undergo a standardized training program focused on the theoretical foundations of the INTERCOG model and the practical application of the protocols. This training is supported by an instructional video series consisting of 21 standardized physical training sessions (one per session) and 9 videos about nutritional advice. To facilitate real-time access during home visits, the workbooks include integrated QR codes that link directly to the corresponding video demonstrations, ensuring uniform delivery of the exercise components [25].

Fidelity is maintained through a multi-layered strategy: (1) digital process logs: interventionists will use REDCap to record session attendance and qualitative execution reports in real-time; (2) clinical supervision: weekly team meetings to discuss implementation challenges; and (3) direct oversight: co-investigators will perform unannounced home visits and follow-up calls to ensure protocol adherence.

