### Statistical methods

Continuous data will be described using means and standard deviations (SDs) or medians and interquartile ranges (IQRs), depending on their distribution as assessed by the Shapiro–Wilk test. These data will be compared between the intervention and control groups via Student’s *t*-test or the Mann–Whitney *U* test, respectively. Categorical data will be summarized using absolute and relative frequencies and compared between groups via the *χ*^2^ test or Fisher’s exact test, as appropriate.

Outcomes will be analyzed across the baseline, 3-, 6-, and 9-month follow-up measurements via generalized linear mixed-effects models (GLMMs). These models will include fixed factors (intervention group, time, and the group × time interaction) and a random effect for participants to account for individual variability. The models utilize maximum likelihood estimation (MLE) methods to handle data that are missing at random (MAR). Potential confounding variables identified during the descriptive analysis were adjusted for. To account for the potential confounding effect of social interaction, perceived social support (measured via the MOS survey) will be included as a time-varying covariate in the models. The results are reported as adjusted mean differences with their respective 95% confidence intervals (95% CIs). Imputation methods will not be used.

Analysis will be performed on both an intention-to-treat (ITT) and per-protocol (PP) basis. To account for multiplicity and reduce the risk of type I error across the various secondary outcomes, *p *values will be adjusted using the Benjamini–Hochberg false discovery rate (FDR) procedure. The level of statistical significance will be set at *α* = 0.05. All statistical analyses will be conducted via STATA 17 (Stata Corporation, College Station, USA).

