### Feasibility analysis and success thresholds

The NPMI INTERCOG viability will be determined by three quantitative benchmarks: recruitment (>70% of eligible candidates), retention (>70% at 9 months), and adherence (>70% session completion). These thresholds account for the high participant burden inherent in multicomponent lifestyle interventions especially in geriatric populations, where age-related attrition is significant factor [63, 64]. Additionally, qualitative acceptability will be evaluated through thematic analysis of semi-structured interviews; also, we will obtain an average satisfaction score (0–5 points) on the participant feedback surveys. The intervention will be deemed feasible for a definitive trial if at least two quantitative targets are met alongside positive qualitative feedback.

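### The post-randomisation elimination rule for nonattendance can act only in the INTERCOG arm, is not reconciled with the ITT analysis, and makes the adherence benchmark almost automatic if eliminated dyads leave the denominator

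*Protocol article*

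**What the plan says.** Participants and eligibility criteria separates the exclusion criteria from a second list, of grounds on which a participant is eliminated from the study. Two of them are "institutionalization of the participant for a period longer than 1 week during the intervention phase, death of the participant during the intervention phase". The third is "nonattendance at 34% or more of the scheduled sessions with professional accompaniment".

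The arms differ in what they are scheduled to attend. Under Intervention, "Patients assigned to the intervention group will receive the NPMI INTERCOG for 12 weeks, twice weekly home-based sessions". For the comparator, "The control group, in addition to usual care, will receive weekly information on the prevention of infectious diseases on their mobile devices". Controls are offered a compressed form of the programme only after the study has ended.

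Statistical methods states that "Analysis will be performed on both an intention-to-treat (ITT) and per-protocol (PP) basis". The models use maximum likelihood under missing at random, without imputation. Feasibility analysis and success thresholds sets three benchmarks: "recruitment (>70% of eligible candidates), retention (>70% at 9 months), and adherence (>70% session completion". Meeting two of the three, together with positive qualitative feedback, is enough to call the intervention feasible. The section does not say whether eliminated dyads stay in the adherence or retention denominators.

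**The concern.** A nonattendance rule can operate only once sessions have been scheduled and missed, so it acts after randomisation. Controls have no accompanied sessions to miss, so it can act in one arm only, and on a behaviour plausibly related to health, cognition and family support. Taken at its word, elimination from the study means that poor attenders leave the INTERCOG arm while comparable controls stay.

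Two results are at stake. The cognitive comparison would set the better attenders against all controls. The adherence rate, which the pilot is meant to deliver for planning a larger trial, would be computed after those who did not adhere had been removed.

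**Working it through.** The article gives no calculation on this point to reproduce. Inputs from it are: 12 weeks at two home sessions a week; the 34% cut; the 70% benchmarks; 51 dyads per group, 15% attrition, a MoCA effect of 0.7 and an SD of differences of 1.8 (Sample size). Attendance distributions and the outcomes of eliminated dyads are assumptions, because the article gives no figures for them.

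**1. The cut against the benchmark**

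- Sessions: 12 × 2 = 24.
- Elimination threshold: 0.34 × 24 = 8.16, so 9 missed sessions (37.5%) trigger it and 8 missed (33.3%) do not.
- Lowest attendance without elimination: 16/24 = 66.7%.
- Next step up: 17/24 = 70.8%, above 70%.

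A dyad that is not eliminated falls short of 70% only if it attended exactly 16 sessions.

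**2. Adherence under the two denominators**

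Each dyad's attendance probability p follows Beta(μk, (1 − μ)k) with k = 1/ρ − 1, where μ is the true mean and ρ the within-person correlation. Sessions attended are Binomial(24, p). A dyad is eliminated if missed/24 ≥ 0.34. The benchmark is read as mean completion above 70% in an arm of 51. Results for ρ = 0.3:

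| True mean | Eliminated | P(pass), all randomised to INTERCOG | Mean among non-eliminated | P(pass), non-eliminated |
|---|---|---|---|---|
| 50% | 65% | 0.00 | 82% | 1.00 |
| 60% | 51% | 0.004 | 84% | 1.00 |
| 65% | 44% | 0.10 | 86% | 1.00 |
| 70% | 37% | 0.51 | 87% | 1.00 |

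Across ρ = 0.1, 0.3 and 0.5 and true means of 50 to 65%, P(pass) is 0.00 to 0.16 on all randomised to INTERCOG and 0.99 to 1.00 on the non-eliminated. If the benchmark instead means the share of dyads above 70% completion, then at a true mean of 60% and ρ = 0.3 that share is 44% of all randomised to INTERCOG and 90% of the non-eliminated.

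**3. Retention**

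Passing needs more than 0.70 × 102 = 71.4, that is 72 dyads, if retention is pooled over arms. With 15% attrition, controls keep 0.85 × 51 ≈ 43. Suppose eliminated dyads count as not retained and INTERCOG has no other loss. At a true mean attendance of 60%, INTERCOG keeps 0.49 × 51 ≈ 25, giving (25 + 43)/102 = 66.7%, a fail. Elimination therefore lowers retention. Under the two-of-three rule, feasibility can still pass on recruitment plus adherence.

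**4. Exploratory cognitive comparison**

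Assume no true effect, that a fraction e of the INTERCOG arm is eliminated and dropped, and that their MoCA change would have been d points worse than that of the rest of their arm. The bias in favour of INTERCOG is e × d, with standard error 1.8 × √(1/51 + 1/[51(1 − e)]).

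- e = 0.10, d = 0.5: bias 0.05 points, 7% of 0.7; two-sided type I error 0.052.
- e = 0.20, d = 1.0: bias 0.20 points, 29% of 0.7; type I error 0.083.
- e = 0.30, d = 1.5: bias 0.45 points, 64% of 0.7; type I error 0.21.

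All accompanied sessions fall within the 12 weeks before the first follow-up at 3 months. If elimination also ends assessment, these dyads have baseline data at most. A likelihood model then cannot recover their outcomes unless the missing-at-random assumption holds given the observed data, and attendance is not among the model terms listed.

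**The case against.** The strongest reply is that the article never says eliminated dyads leave the ITT set or lose their 3-, 6- and 9-month visits. It promises both ITT and per-protocol analyses, and a cut near two-thirds attendance is a natural per-protocol definition. Analysis sets are commonly defined in the SAP or full protocol. Table 2 records people who decide not to continue, completion rates and reasons for non-compliance, which suggests that non-completers will be counted somewhere. Cognitive efficacy is declared exploratory, and adherence is only one of three quantitative benchmarks.

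Much of this stands, and it makes the harm conditional. It does not remove the problem, because the article does more than leave a definition open: it states a rule under the name of study elimination and says nothing to confine it to the per-protocol set.

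A reader might infer more than the text supports:

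- That all three elimination grounds act in the intervention arm only. Death and institutionalisation are worded for any participant; only nonattendance is arm-specific.
- That the ITT analysis is certainly broken. This follows only if eliminated dyads are not followed or not analysed.
- That retention is biased upwards. Eliminated dyads would ordinarily count as lost, which lowers it, so the retention benchmark is a partial guard.
- That the session count contradicts itself, because the fidelity section mentions "21 standardized physical training sessions (one per session". That figure describes the physical-training video series, and the session schedule is in Supplementary Table S1, which is not shown. No mismatch is established.

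**Conclusion.** The concern holds in conditional form. The nonattendance criterion is a post-randomisation rule that can remove dyads only from INTERCOG, and the article does not reconcile it with its ITT commitment. If followed literally, it favours INTERCOG in the exploratory cognitive comparison, by 0.05 to 0.45 MoCA points for 10 to 30% eliminated with changes 0.5 to 1.5 points worse. Those ranges are assumptions.

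The firmer result is for adherence, because it follows from the article's own thresholds: the floor among non-eliminated dyads is 66.7% against a target above 70%. Computed on those dyads, the benchmark cannot tell a well-attended programme from a poorly attended one. Computed on all dyads randomised to INTERCOG, it can. Nothing in the article fixes which will be used. Recruitment is already open, and assessments not made on eliminated dyads cannot be recovered later by an analysis plan.

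**What to change.** - Reword the nonattendance criterion as intervention non-completion instead of elimination from the study.
- Continue the 3-, 6- and 9-month assessments for every randomised dyad whatever its attendance, where still possible, and keep all of them in the ITT set.
- Use the 34% cut only to define the per-protocol set.
- Compute adherence on all dyads randomised to INTERCOG and retention on all randomised dyads, with death counted as not retained and reported by arm.

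The cost is a few sentences of protocol wording and keeping already scheduled visits for non-attenders. Reported adherence may be lower than it would be among the remaining dyads alone.
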